**B. Study Outcome measure(s)**

The primary outcomes are:

1. SMC coverage for the determination of the optimal mode of delivery during Year 1. SMC coverage will be defined as proportion of the children who have received the three treatments doses at each of the three rounds of SMC.
2. Incidence of the clinical malaria for the optimal frequency of SMC in Year 2. Clinical malaria will be defined as signs and symptoms suggestive of malaria with positive RDT and/or positive blood smear.

Secondary trial outcomes of the study include:

1. Parasite prevalence defined as the proportion of children with a positive malaria blood smear and parasite density measured in Years 1, 2 and 3.
2. Prevalence of moderate anemia defined as hemoglobin concentration < 8 g/dL measured by hemoglobin analyzer.
3. Cellular and humoral antimalarial immune responses to malaria parasites.
4. Levels of cytokines and other host responses measured in sera/plasma or in immune cells.

5. Frequency of mutations at codons 51, 59, and 108 of the dhfr gene, 437 and 540 of the dhps gene, codon 76 in the *P. falciparum* chloroquine transporter gene (pfcr), and codon 86 of the *P. falciparum* multidrug resistance gene one (pfmdr1)

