### ***Interventions***

SMC will consist of the administration of full treatment courses of sulfadoxine-pyrimethamine plus amodiaquine (SP+AQ) at monthly intervals during the peak of the malaria transmission season (August – through October or November depending on the year of the study and study arm). During each round, children aged 3–11 months will receive 75 mg of AQ given once daily

for 3 days plus a single dose of 250/12.5 mg of SP, while children aged 12–59 months will received 150 mg AQ base given once daily for 3 days and a single dose of 500/25 mg of SP. The single dose of SP will be given only on the first day, at the same time as the first dose of AQ. Children will be observed for 30 minutes after drug administration. If vomiting occurs during this period, drugs will be re-administered. If vomiting recurs this will be noted but the drugs will not be given on a third occasion. Such children will not be excluded from the trial and they will be eligible to receive drugs at the subsequent monthly treatment.

In villages assigned to door –to-door delivery (DDD), community health workers (CHW) will visit each compound to administer SMC drugs. In the villages assigned to fixed point distribution (FPD), children will receive SMC at a central fixed point in the village. The administration of the three days treatments at each round will be done by the CHW for children assigned to directly observed therapy (DOT) while for children assigned to non-directly observed therapy (NDOT), the treatment of first day will be given by the CHW and treatments for second and third days will be given by the caregiver at home for each round. SMC will be implemented using standardized field implementation guidelines developed by the WHO [WHO 2013] adapted to the situation in Mali. Monitoring and evaluation tools for SMC will be developed and integrated with the health system in Mali.

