### **Patient Safety Considerations**

Risks to participants in the trial are small. The trial will use only licensed products and does not involve any new methods. Over 800,000 courses of SP and AQ have been given for SMC without any report of a drug associated severe adverse event (SAE) including when enhanced surveillance was used [Wilson et al 2011, Ndiaye et al . submitted]. Neither the less the serious adverse events will be monitored throughout the study period and any SAE related to the study

drugs will be reported to the Ethical Committee of the Faculty of Medicine, Pharmacy and Dentistry of the University of the Bamako and the within 24 hours the Principal Investigator has become aware of it.

*Definitions and Procedures for recording and reporting Adverse Events (AE) and Serious Adverse Events (SAE)*

An adverse event (AE) is defined as any clinical symptom or sign that occurs in study children after administration of the study drugs that may or may not have a causal relationship with the study drugs. A serious adverse event (SAE) is any clinical condition that fulfils at least one of the following criteria: results in death, is life-threatening (the child was at risk of death at the time of the adverse event), results in disability/incapacity. AE and SAE will be classified by severity, causality and outcome as described below

*Severity.* The severity of a clinical adverse event is to be scored according to the following scale:

- Mild: Awareness of sign or symptom, but easily tolerated.
- Moderate: Discomfort enough to cause interference with usual activity.
- Severe: Incapacitating with inability to perform usual activity.
- Life-threatening: Patients at risk of death at the time of the event.
- Death

*Assessment of Causality and Outcome.* The relationship between the study drugs and the occurrence of each AE/SAE will be determined based on their clinical judgment. Alternative causes, such as the natural history of the underlying diseases, concomitant therapy, other risk factors, and the temporal relationship of the event to the study drug will be considered and investigated. The relationship of an adverse event to study drug is to be assessed according to the following definitions:

- Definitely unrelated: events that had occurred prior to administration of the study drugs or events that are obviously unrelated to the study (e.g. accidental injury).

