### **C. Final Analysis Plan**

*Describe statistical methods that will be used to analyze data.*

Data will be entered and verified using DataFax. The cleaned database will be exported to Stata (Houston Texas USA) or SAS for analysis. An intention-to-treat analysis will be used except for the immunological endpoints for which the exact number of the SMC treatments received will be considered.

SMC coverage will be determined using the information on the SMC card and from interview of parent or care giver and will be determined as the proportion of children who received all the treatments at all the SMC rounds during the transmission season. The proportion of children who received at least the first treatment dose of the SMC will be also estimated as secondary endpoints for SMC coverage. SMC coverage will be compared between arms and years of

interventions with 95% confidence intervals adjusted for cluster design (using cluster option in Stata for example). The DDD+NDOT arm will be considered as control group.

The census of the children will be updated at each round and at the end of the transmission season to allow a good estimation of person-time of follow-up. Cases of the clinical malaria will be recorded and the incidence rate of the clinical malaria defined as the number of clinical malaria episodes divided by total child days at risk. Children will not be considered at risk 21 days after a clinical malaria episode. Incidence rates of clinical malaria will be compared between treatment arms using generalized estimating equation to estimate the incidence rate ratio, with adjustment for age, previous SMC regimens and the lack of independence among repeated episodes in the same child.

Proportions of other secondary endpoints such as parasite prevalence, prevalence of anemia and frequency of molecular markers of resistance to SP and AQ and adverse events associated with study drugs will be estimated and compared between groups using generalized linear models with 95% confidence intervals, adjusted for cluster design and potential confounding variables such as age and use of ITN.

Differences at baseline will be compared using Chi-squared or Fisher's exact tests as appropriate for categorical variables and by analysis of the variances for quantitative variables that are normally distributed. Nonparametric tests will be used for non-normally distributed data.

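### The planned between-arm comparison of adverse events is liable to show DOT as less well tolerated than NDOT, because detection opportunities differ by arm and no common collection is described

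*Protocol*

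**What the plan says.** Section 5.C (Final Analysis Plan) groups drug-associated adverse events with the other secondary endpoints and says that "adverse events associated with study drugs will be estimated and compared between groups using generalized linear models", with estimates "adjusted for cluster design and potential confounding variables such as age and use of ITN". The French version (5.3) says the same.

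The Interventions text in section 4 has the health worker give all three days of each round in DOT villages. In NDOT villages the worker gives day 1, and "treatments for second and third days will be given by the caregiver at home for each round". Drugs and age-based doses do not differ by arm. The same text says, without qualification, that "Children will be observed for 30 minutes after drug administration", with re-administration after a first vomiting and a note of any second one. It names no observer for doses given at home.

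Patient Safety Considerations defines an adverse event as "any clinical symptom or sign that occurs in study children after administration of the study drugs" and sets out grading of severity, causality and outcome. Only serious events are said to be monitored throughout. The section does not say how, when or by whom non-serious events are collected. In the follow-up section, passive surveillance is aimed at clinical malaria, and the end-of-season survey covers coverage, infection, anaemia and immunology.

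**The concern.** A comparison of recorded adverse events is interpretable only if an event has a similar chance of being recorded in each arm. Here that chance may depend on the randomised intervention itself. A worker who returns on days 2 and 3 can see vomiting after those doses and can hear about reactions to the previous day's dose. An NDOT child has no further scheduled dosing contact until the next round. Adjusting for age, bednet use and clustering cannot remove a difference in detection that is tied to the arm.

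Intake adds a second problem. The assigned drugs are identical, but home doses may be missed. Fewer doses swallowed in NDOT would produce a real difference in the same direction, so a recorded gap would mix the two causes. At stake is a stated safety comparison that could be reported as a tolerability difference between delivery methods when it may be nothing of the kind.

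**Working it through.** The protocol gives no adverse-event rate, sample size or power, so there is no stated figure to reproduce.

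**Contacts (Interventions; section 3.B for the three Year 1 rounds).**
- DOT: 3 days × 3 rounds = 9 scheduled worker-given dosings.
- NDOT: 1 day × 3 rounds = 3.
- Ratio 9/3 = 3.

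**Upper bound.** Suppose events on home-dosing days are never captured and contact-day capture is the same in both arms. If a share d of events follows the day 1 dose, the ratio of recorded events is 1/d.
- d = 1/3 (equal risk each day): 3.0.
- d = 0.6 (an assumption; SP is given only on day 1): 1/0.6 = 1.67.

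**Partial capture.** Assumptions not in the protocol: true risk q of 0.01 to 0.05 per dosing day, equal in both groups; detection 0.8 on a contact day and b on a home-dosing day; all doses taken. The proportions of children with at least one recorded event are:
- DOT: 1 − (1 − 0.8q)^9
- NDOT: 1 − (1 − 0.8q)^3 × (1 − bq)^6

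Example, q = 0.03 and b = 0.4: DOT 1 − 0.976^9 = 0.196; NDOT 1 − 0.976^3 × 0.988^6 = 0.135; ratio 1.45.

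**Chance of a false finding that DOT is worse.** For illustration only, I borrow the coverage-survey figures in 5.A: 446 per arm, at least 10 clusters per arm, intraclass correlation 0.01.
- Design effect: 1 + (44.6 − 1) × 0.01 = 1.436.
- Two pooled arms: 2 × 446 = 892; effective size 892/1.436 ≈ 621 per group.
- Two-sided 5% test of two proportions. In the example: SE = √[(0.196 × 0.804 + 0.135 × 0.865)/621] ≈ 0.021; 0.061/0.021 ≈ 2.9; 2.9 − 1.96 ≈ 0.95; probability about 0.83.

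| Home-day capture b | DOT/NDOT ratio (q 0.01–0.05) | Chance of false DOT-worse result |
|---|---|---|
| 0 | 2.67–2.93 | 0.97–1.00 |
| 0.2 | 1.84–1.97 | 0.77–1.00 |
| 0.4 | 1.42–1.48 | 0.40–0.96 |
| 0.6 | 1.17–1.19 | 0.13–0.41 |
| 0.8 (equal) | 1.00 | 0.025 (nominal) |

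**Intake alone.** With equal capture (0.8 on every day), q = 0.03 and a fraction a of home doses taken, replace bq by 0.8aq. The ratio is 1.33 at a = 0.6 and 1.14 at a = 0.8. Moderate non-adherence can thus give a ratio of the same order as partial under-detection, and the recorded data cannot tell them apart.

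**The case against.** The strongest reply is that the protocol never says adverse events are collected at dosing contacts. The 30-minute observation serves vomiting and re-administration, and collection procedures may sit in SOPs, standard forms or a statistical analysis plan not shown. If events came only through passive reporting or a common enquiry, the bias could be small or absent. This stands, and it limits the point to a liability. A reader might infer that DOT is bound to look worse; the documents do not establish that. What survives is that the comparison is stated, the contacts are unequal, and nothing in the protocol equalises capture.

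A reader might also take a ratio of 3 as the expected size. It is a ceiling: it needs zero capture on home-dosing days, and the count of 9 needs every DOT child to attend every dosing, although complete receipt is itself the coverage outcome.

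Nor do identical drugs imply that any gap would mainly reflect contacts. Differential intake is a real alternative under intention to treat.

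Finally, a reader might suppose that safety would sway the choice of delivery method. Sections 4.A and 5.B rest that choice on coverage and then malaria incidence, with the simplest method as fallback if neither differs significantly. Adverse events are also absent from the outcome list in 3.B. The imbalance does not affect the Year 2 comparison of three with four rounds, where both arms share one delivery mode.

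**Conclusion.** The point holds as a minor one. The protocol states a between-group comparison of adverse events whose detection opportunities are 9 to 3 by arm in Year 1, with an adjustment that cannot correct this and no common collection described. DOT is liable to look less well tolerated, and a gap could not be assigned to detection or to intake. The ratio of recorded events lies between 1 (equal capture and intake) and about 3 (no home-day capture), or about 1.7 at most if 60% of events follow day 1. The direction rests on capture being better on contact days; the intermediate figures rest on the assumed risks and detection probabilities. The consequence is a misleading secondary safety comparison. The documents do not support a consequence for the choice of delivery mode.

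**What to change.** In 5.C, limit the Year 1 DOT v NDOT comparison of adverse events to those captured the same way in every arm:
- the observation directly after the worker-given day 1 dose;
- events presenting at health facilities;
- one identical caregiver question, asked in all arms at each census update, about events since the previous round's treatment.

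Include the end-of-season census update, which 5.C already plans, so that the last round is covered. Report DOT day 2-3 observations descriptively, and state that differential intake may contribute to any gap. With equal capture and full home intake, the expected ratio returns to 1.00 and the chance of a false DOT-worse result to the nominal 2.5%.

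Separately, the unqualified 30-minute observation statement in Interventions and the home dosing on days 2 and 3 in NDOT must be reconciled; which way is for the sponsor.

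The cost is a short edit to the analysis text and one question at contacts already scheduled. The downside is that recall over about a month is less exact for mild events, and may not be perfectly equal across arms, since caregivers seen three times per round may report differently from those seen once.

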#### ***Census and randomization***

Once community consent to the trial is obtained, a household census will be conducted and all households within the study areas with children under 5 years of age will be identified. At the time of census, a preliminary screening of potentially eligible children will be undertaken. Eligible children will be identified and written informed consent will be obtained from their caretakers for their inclusion in the trial. Children entered into the trial will be assigned a unique ID number and their demographic data (date of birth and/or age, and gender) will be collected.

The census will be updated at each SMC round and potentially eligible participants (such as children who did not reach the age of three months during the previous round) will be identified and screened for eligibility and enter into the study. This updated census will collect information on migration and death of children enrolled into the study for precise estimation of person-time of follow-up.

The unit of randomization will be village and all eligible children in a village will be allocated to the same study arm (DDD+ DOT or DDD+NDOT or FPD+ DOT or FPD + NDOT) to avoid confusion in Year 1. Villages in the selected sub-districts will be randomized at 1:1 ratio to receive either a door –to-door delivery (DDD) or fixed point distribution (FPD) of SMC. They will also be randomized to receive SMC as directly observed therapy (DOT) or a non-directly observed therapy (NDOT). In Year 2, villages in the two newly randomly selected districts will be randomized into two groups to receive either three or four rounds of SMC.

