## 5. Statistical Considerations and Data Analysis

### A. Sample Size and Power Calculation(s)

*Cross-sectional surveys.* Sample size for cross-sectional surveys will be based on the SMC coverage. Assuming 60% average coverage of SMC by the combination of nonoptimal methods (pools of two groups), 300 children/arm will be needed to detect 10% increase in average coverage for two pooled groups with at least 85% power correcting for multiple tests and using two Fisher's exact tests. To account for cluster sampling with a minimum 10 clusters per arm, interclass correlation of 0.01 (based on a previous trial showing vaccine coverage (Dicko et al BMC Pub Health 2011), and 5% missing data, 446 children will be surveyed per group (total of 1784 children).

*Passive surveillance.*

Assuming a clinical malaria attack rate of 0.3 per child per year in “3 rounds” arm, to detect an absolute difference in attack rate of the 0.075 episode/chil/ year (corresponding to 25% reduction) in the “4 rounds” arm, with a one sided p-value of 0.025 and power of 80%, using a quasi poisson model accounting for 20 equally sized clusters per arm with intraclass correlation of 0.01 and 5% missing data we will need 1386 per arm, or 2,772 subjects total.

*Immunological parameters.* We will base our sample size calculations for immunological endpoints on the humoral immune response to AMA1. We select this response because AMA1 is highly immunogenic from among malaria antigens. Also, the intervention in this trial is directed at reducing the blood stage burden of parasites during the malaria season, and the response to AMA1 reflects exposure to blood stage forms of the parasite. In earlier serology studies of young children participating in an AMA-1 vaccine trial in Bancoumana, Mali (Sagara et al, Vaccine, 2009), we observed the peak antibody titer against AMA1 to occur near the end of the malaria season (among children receiving control vaccine), with geometric mean antibody levels of 120 antibody units (95% CI, 70-205). Antibody levels just prior to the start of the malaria season (before vaccination) were 40 (25-75) antibody units. Based on these data, 467 subjects per

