Les différences au niveau de référence seront comparées en utilisant le test de Chi -carré ou Fisher exact pour les variables qualitatives et par l'analyse de la variance pour les variables quantitatives qui sont normalement distribués. Les tests non paramétriques seront utilisés pour les variables qui n'ont pas une distribution normale.

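### Baseline differences between village-randomised arms are to be tested at child level with no cluster adjustment, so the baseline p-values will be too small (about 1.5 to 2.8 times too many false positives at the protocol's own ICC)

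*Protocol*

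**What the plan says.** Under Census and randomization the protocol states: "The unit of randomization will be village and all eligible children in a village will be allocated to the same study arm". In Year 1 there are four delivery arms; in Year 2, villages in two new sub-districts are allocated to three or four rounds.

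The last paragraph of C. Final Analysis Plan reads: "Differences at baseline will be compared using Chi-squared or Fisher's exact tests as appropriate for categorical variables", and continues "by analysis of the variances for quantitative variables that are normally distributed", with nonparametric tests otherwise. The French section 5.3 repeats it: "Les différences au niveau de référence seront comparées en utilisant le test de Chi -carré ou Fisher exact pour les variables qualitatives". Neither version mentions clustering at this point.

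Elsewhere in the same section clustering is handled. Confidence intervals for SMC coverage are adjusted for the cluster design, and the secondary endpoints are compared with generalised linear models "adjusted for cluster design and potential confounding variables such as age and use of ITN". The sample-size section also allows for it: "To account for cluster sampling with a minimum 10 clusters per arm, interclass correlation of 0.01".

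**The concern.** A baseline test in this trial should ask whether the arms differ by more than random allocation of villages would produce. Pearson chi-squared, Fisher's exact, one-way analysis of variance and rank tests on individual children take their reference distribution from independent children. When children in a village resemble each other, arm totals vary more than that distribution allows, and a sound randomisation is flagged as imbalanced too often.

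The plan is inconsistent with itself here. Parasite prevalence and anaemia are compared with cluster adjustment as endpoints, but the sentence on baseline differences offers only unadjusted tests. The protocol names specific tests and they do not fit its design, so this is not simply detail left for an SAP. At stake is the credibility of the baseline table: readers could see several small p-values and doubt an allocation that worked.

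**Working it through.** **Inputs from the protocol**
- Year 1: four arms, at least 10 villages per arm, 446 children surveyed per arm, so 446/10 = 44.6 per village.
- Year 2: two arms, 20 villages per arm. Baseline data come from a cross-sectional survey.
- Village ICC 0.01, which the protocol describes as an "interclass correlation of 0.01 (based on a previous trial showing vaccine coverage". No ICC is given for any baseline variable.

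**Assumptions**
- Nominal two-sided 5% level for the baseline tests (none is stated).
- The Year 1 baseline subset has the survey size of 446 per arm.
- The Year 2 survey also has 446 per arm, spread over 20 villages: 446/20 = 22.3 per village.
- Equal village sizes.

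**Step 1: reproduce the survey size.** Start from 300 per arm and inflate for 10 clusters at ICC 0.01:

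n = 300 × [1 + (n/10 − 1) × 0.01] = 297 + 0.3n, so n = 297/0.7 = 424.3.

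With 5% missing: 424.3/0.95 = 446.6, against the stated 446. The cluster size and ICC used below are therefore those behind the protocol's own figure.

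**Step 2: actual error of the child-level test.** With m children per village, the design effect is DE = 1 + (m − 1) × ICC. The unadjusted statistic behaves approximately as DE times a chi-squared variable, so

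actual error = P(χ²_df > c_df / DE), with c₁ = 3.841 (two groups) and c₃ = 7.815 (four arms).

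| Setting | m | ICC | DE | c/DE | Actual error | Multiple of 5% |
|---|---|---|---|---|---|---|
| Year 1, four arms | 44.6 | 0.01 | 1.436 | 5.442 | 14.2% | 2.8 |
| Year 1, two groups | 44.6 | 0.01 | 1.436 | 2.675 | 10.2% | 2.0 |
| Year 2, two arms | 22.3 | 0.01 | 1.213 | 3.167 | 7.5% | 1.5 |
| Year 1, four arms | 44.6 | 0.05 (assumed) | 3.180 | 2.457 | 48.3% | 9.7 |
| Year 1, two groups | 44.6 | 0.05 (assumed) | 3.180 | 1.208 | 27.2% | 5.4 |
| Year 2, two arms | 22.3 | 0.05 (assumed) | 2.065 | 1.860 | 17.3% | 3.5 |

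At ICC 0 there is no inflation.

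**Step 3: check by simulation.** Beta-binomial villages with the plain chi-squared test (20,000 runs per setting, 45 children per village, ICC 0.01) gave 14.3–14.6% for four arms and 10.0–10.4% for two groups. Child-level analysis of variance (50,000 runs) gave 14.5% and 10.4%.

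**Step 4: check the remedy.** An F test on village proportions in the same two settings at ICC 0.01 rejected in 5.1% of runs with four arms and 5.1% with two groups. The nominal level is restored.

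**The case against.** Three objections carry weight.

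**Size.** A reader might infer inflation of three to seven times across the board. The documents do not support that.
- For Year 2, 1,386 children per arm (69.3 per village) would give 13.1%, but that is the passive-surveillance size. The protocol takes Year 2 baseline parasitaemia, resistance markers and immune responses from a cross-sectional survey.
- For Year 1, spreading half of the 10,800 children evenly over 40 villages (135 each) would give 34.2% at ICC 0.01. But the demographic data listed for the census are age or date of birth and gender, which should cluster little. At an assumed ICC of 0.001 the census figure is about 7.5% (DE 1.134). Blood-based variables come from a subset.
- Ten villages per arm is a minimum. More villages for the same number of children would lower the figures.

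**Harm.** A reader might also infer that false imbalances would drive the choice of covariates and bias the results, because the list of confounders is introduced by *such as*. The protocol does not say this. It names age and previous SMC regimens for incidence, and age and ITN use as examples for the secondary endpoints; nowhere does it select covariates by baseline p-value. Delivery mode is chosen on coverage and then incidence, and frequency on incidence.

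**Scope.** Planned Interim Analyses already describes the baseline immunological parameters and resistance markers as a descriptive analysis, so part of the baseline work may never be tested.

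These points reduce the size and consequence of the problem. They do not make the named tests valid for village-randomised arms, and the section's general use of cluster adjustment is not extended to this sentence.

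**Conclusion.** The baseline sentence is wrong as written: it names child-level tests for arms formed by randomising villages. At the protocol's ICC of 0.01 and an assumed 5% level, false positives run at about 14% (four arms) and 10% (two groups) in the Year 1 survey. In Year 2 they run at about 7.5% if 446 per arm are surveyed in 20 villages. That is roughly 1.5 to 2.8 times nominal. Variables with stronger village correlation would exceed this range, and age and sex would barely be affected. The ICC of 0.01 was taken from vaccine coverage, so its fit to parasitaemia, anaemia or ITN use is unknown.

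The consequence is a baseline table with misleading p-values. No primary comparison, choice of delivery mode or frequency, or stopping rule depends on these tests, so the point does not call the primary results into question. It is worth correcting because the error is clear and the correction is nearly free.

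**What to change.** Replace the baseline sentence in C. Final Analysis Plan, and its French counterpart in 5.3, with wording such as: *Baseline characteristics will be summarised by arm at child and village level, without significance tests.*

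If p-values are to be kept, state that they will use the village-cluster adjustment already planned for the endpoints: a generalised linear model with clustering by village, a Rao-Scott chi-squared test, or a test on village-level summaries.

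The cost is one sentence in each language version and no new data. The only downside is that baseline p-values will be fewer or larger.
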